#### **EXPECTEDNESS OF SAEs**

There are no specific expected SAEs from participation in whole body PET/MRI or dedicated MRI imaging.

Incidental abnormalities detected on imaging will be discussed between the reporting radiologist, study doctor, principal investigator and participant. If required, further review will be arranged by referral to the general practitioner or appropriate specialist. Any incidental findings are expected to be asymptomatic and unpredictable, given the study population of otherwise well, healthy adult volunteers.

There are no commonly reported adverse reactions to radiopharmaceuticals and  $^{18}\text{F}$  FDG in the literature (Appendix G). A multicenter review of radiopharmaceutical use (including  $^{18}\text{F}$  FDG) administrations found an AE incidence rate of 2.1 per 100 000 administrations [12]. A single case of a probable cutaneous adverse drug reaction has been reported in an individual with multiple existing drug allergies [13]. This did not preclude the patient from repeated dosing. A single case episode of possible anaphylaxis has been reported in the context of the administration of multiple other medications [14]. In both cases symptomatic treatment was effective. Based on the volume of  $^{18}\text{F}$  FDG use in the clinical setting, and paucity of published adverse events, the risk of such events is considered to be extremely low.

### **8.5 Recording and Prompt Reporting of Events**

In all cases of AEs, the reporting process used for the MAIN study from which the participant was recruited will be used. If MAIN study procedures are not available recording and reporting of AEs will be in accordance with QIMRCTSOP013 and QIMRCTSOP016.

Any AE deemed related to the administration of  $^{18}\text{F}$  FDG or other imaging procedures will be discussed where possible to further clarify causality with the nominated Nuclear Medicine Independent Medical Advisor.

Any SAE deemed related to the administration of  $^{18}\text{F}$  FDG or other imaging procedures will be reported to the Sponsor within 24 hours following discussion with the medical monitor and where possible with the nominated Nuclear Medicine Independent Medical Advisor. The TGA and any other relevant authorities will be notified by the Sponsor (or institutionally approved representative) within 72 hours as per existing TGA guidelines.

### **REPORTING OF PREGNANCY**

Female participants of child bearing potential will undergo pregnancy testing as outlined and as per MAIN study protocol. All pregnancy-related policy and procedures will be managed as per MAIN study protocol in addition to exclusion from further EXPLORATORY STUDY participation.

If the MAIN study from which EXPLORATORY STUDY participants only recruits women of non-childbearing potential, no point of care testing or pregnancy monitoring will take place.

### **8.6 Halting Rules**

The investigator(s) reserve the right to halt the study at any point. There are no specific safety findings expected that may prompt suspension or termination of the EXPLORATORY STUDY. In a situation where the MAIN study is halted, the EXPLORATORY STUDY will also be halted as required.

## **9. QUALITY ASSURANCE**

EXPLORATORY STUDY materials and quality assurance related to the imaging of participants and any involvement onsite at HIRF will take place as per existing

HIRF/RBWH processes. Data quality will be considered and described in the presentation of results.

The MAIN study is a registered clinical trial employing an external study monitor responsible for quality assurance with respect to inoculum and participant safety (including pathology testing and clinical examination/investigations.)

## **10. STATISTICAL CONSIDERATIONS**

### **10.1 Sample Size**

This is a pilot investigation to assess the application of advanced medical imaging in subpatent malaria. The population will comprise of eight adults (male and non-pregnant, non-lactating female participants between 18 and 55 years of age, recruited from the IBSM model MAIN study population.

It is expected that this study will be hypothesis generating. There are no pre-existing PET or prospective MRI imaging trials in malaria published in the literature. Data from this pilot investigation may be used in future power calculations if required.

### **10.2 Statistical Analysis Plan**

All data will be presented descriptively. Pre and post inoculation quantitative imaging metrics will be compared with paired T-tests or Mann-Whitney U tests (statistical significance  $p < 0.05$ ). Imaging results may be described with respect to demographic, clinical and biochemical data collected as part of the MAIN study.

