## **ii. Study Outcome Measures**

### **Primary**

The primary objective of the study is to assess the application of whole body  $^{18}\text{F}$  FDG-PET/MRI in describing the parasite biodistribution and biomass in subpatent malaria. This is a hypothesis generating pilot investigation expected to have predominately descriptive outcomes.

The primary outcome measures will be the quantified and semi-quantified  $^{18}\text{F}$  FDG uptake values from specific regions of interest. Regions of interest for quantification of uptake will be spleen, bone marrow (lumbar spine and/or pelvis), muscle bulk (quadriceps) and brain. Post inoculation measurements will be compared to baseline pre inoculation uptake values. Biochemical markers of parasitaemia and total biomass from MAIN study data will be compared to  $^{18}\text{F}$  FDG uptake values.

Any other regions of interest (as deemed by the investigators) identified after imaging will have semi-quantified  $^{18}\text{F}$  FDG uptake values calculated for further comparison.

The other primary objective seeks to apply advanced MRI techniques to early *Plasmodium* infection. This will generate descriptive outcomes and inform future MRI sequence selection to optimize imaging in malaria.

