### **3. STUDY DESIGN**

This is an EXPLORATORY STUDY comprising a population recruited from single-center, IBSM model MAIN studies. The population will consist of up to eight healthy adults inoculated with *Plasmodium* species parasite from existing MAIN study population.

MAIN study refers to the parallel IBSM MAIN study from which the participant is drawn from.

Participants will receive **two** scans: the first within one week prior to MAIN study inoculation and the second one to two days prior to confinement with peak parasitaemia post BSP inoculation (estimated InD 6 to 7 for *P. falciparum* and InD 8 to 9 for *P. vivax*). Blood samples will be collected at MAIN study timepoints, with no

additional collections planned for the EXPLORATORY STUDY.

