**Evaluation of data:**

All data will be presented descriptively. Pre and post inoculation quantitative imaging metrics will be compared with paired T-tests or Mann-Whitney U tests. *Plasmodium spp.* groups will be compared with unpaired T-tests with consideration of T-value adjustment for population size and Mann-Whitney U tests. Any groups identified based on imaging results will be described with respect to demographic, clinical and biochemical data collected as part of the MAIN study.

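### Mann-Whitney U is offered for pre/post scans of the same people; it ignores the pairing, is conservative, and loses power by an amount the documents cannot fix

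*Supplement*

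**What the plan says.** This concerns the eight-participant protocol (ACTRN12616001238460).

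- **Design.** Section 3 gives every participant two scans: "the first within one week prior to MAIN study inoculation and the second one to two days prior to confinement with peak parasitaemia". Under Study Outcome Measures, the primary outcome is FDG uptake in named regions, and "Post inoculation measurements will be compared to baseline pre inoculation uptake values".
- **Pre/post test.** Section 10.2 states: "Pre and post inoculation quantitative imaging metrics will be compared with paired T-tests or Mann-Whitney U tests". Section 3 (Evaluation of data) has the same sentence. Only 10.2 adds the 0.05 threshold. Sidedness is not stated.
- **Species comparison.** Section 3 continues that the *Plasmodium* species "groups will be compared with unpaired T-tests with consideration of T-value adjustment for population size and Mann-Whitney U tests". Here the groups are independent, so this is a separate statement from the pre/post one.
- **Size.** Section 10.1: "The population will comprise of eight adults". Section 3: "The population will consist of up to eight healthy adults inoculated with" the parasite, so fewer pairs are possible.

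Neither section says when the paired t-test and when Mann-Whitney applies. The documents give no within-person correlation, standard deviation, effect size or power calculation.

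**The concern.** The design lets each person serve as their own control, which removes stable differences between people from the comparison. Mann-Whitney U puts those differences back: it ranks the pre and post values as if they came from two unrelated groups. When a person's two scans are positively correlated, the test's null distribution is too wide for the data, so it rejects too seldom under no change and has less power under a real one.

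The choice is left open. With eight or fewer participants normality cannot be checked convincingly, so an analyst may well turn to the non-parametric option, and that is the one that does not fit the design. It bears on the comparison with baseline that defines the primary outcome. Section 10.1 also says the data may inform later power calculations. Those need the mean within-person change and its SD, and an unpaired rank test supplies neither.

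**Working it through.** The plan states no power or correlation, so there is no figure of its own to reproduce.

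**Inputs from the documents.** Eight pairs (10.1); alpha 0.05 (10.2).

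**Assumptions.** Two-sided testing; bivariate normal data with equal variance before and after; within-person correlation ρ from 0 to 0.9; shifts in units of the cross-sectional SD.

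**1. Why pairing matters.** The variance of the mean difference is 2σ²(1−ρ)/n when pairing is respected and 2σ²/n when it is ignored. Ignoring it overstates the standard error by 1/√(1−ρ): 1/√0.7 = 1.20 at ρ = 0.3, 1/√0.5 = 1.41 at 0.5, and 1/√0.3 = 1.83 at 0.7. The rank tests follow the same pattern.

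**2. Rejection rate with no true change (nominal 5%), Mann-Whitney, n = 8, simulated:**

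| ρ | rejects |
|---|---|
| 0 | 4.8% |
| 0.3 | 2.2 to 2.5% |
| 0.5 | 1.2% |
| 0.7 | 0.2 to 0.4% |
| 0.9 | 0.02% |

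Ranges show repeat simulations.

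**3. Power, n = 8, shift 0.8 SD:**

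| ρ | Mann-Whitney | signed-rank | paired t |
|---|---|---|---|
| 0.3 | 28% | 31% | 37% |
| 0.5 | 26% | 44% | 51% |
| 0.7 | 26% | 64% | 70% |
| 0.9 | 24% | 98% | 99% |

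Repeat runs move these entries by one or two percentage points.

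**4. Larger shift, 1.5 SD, n = 8.** Mann-Whitney against paired t: 80% against 86% at ρ = 0.3, 83% against 95% at 0.5, 87% against more than 99% at 0.7, and 90% against 100% at 0.9.

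**5. Effect set so that the paired t has 80% power.** This needs a standardised change of 1.156, that is a shift of 1.156 × √(2(1−ρ)) SD. Signed-rank then has 73 to 74% at every ρ. Mann-Whitney has 83% at ρ = 0, 73% at 0.3, 57% at 0.5, 48% at 0.6, 34% at 0.7, 19% at 0.8 and 5% at 0.9. At ρ = 0.6 the share lost is 1 − 0.475/0.801 = 41%; at 0.7 it is 1 − 0.338/0.798 = 58%. The loss passes one half at about ρ = 0.65.

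**6. Limit of the replacement.** The smallest two-sided exact signed-rank p is 2/2ⁿ: 2/256 = 0.0078 at n = 8, 2/64 = 0.031 at n = 6, 2/32 = 0.0625 at n = 5 and 2/16 = 0.125 at n = 4. With five or fewer pairs it cannot fall below 0.05.

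**The case against.** The best defence has four parts.

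- **The paired t-test is named first.** Harm arises only if Mann-Whitney is chosen instead. This stands, and it limits the size of the point. It does not remove it, because no rule governs the choice.
- **The error is conservative.** With positive correlation, Mann-Whitney gives fewer false positives, not more. This stands too; the risk is a missed change.
- **The study is a hypothesis-generating pilot with mainly descriptive outcomes.** No power claim or decision rule rests on the p-value. This lowers the severity, but 10.2 does set a significance threshold, and the named test should then suit the data.
- **Power loss depends on unknowns.** A reader might infer that Mann-Whitney throws away most of the power, or that a real change would probably be missed. The documents do not support that. It needs both a correlation above about 0.65 and a moderate effect; at ρ = 0.3 the loss is modest, and with a 1.5 SD shift it is modest even at high ρ.

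Three other inferences go too far. The pre/post contrast is not the only test planned, since section 3 also plans species comparisons. The phrase "with consideration of T-value adjustment for population size and Mann-Whitney U tests" in that species sentence is undefined; it might mean small-sample degrees of freedom or a Welch-type correction, so it can be queried but not called invalid. And the two-participant protocol (ACTRN12616001458426) carries the same wording, but the figures for eight pairs do not transfer: with two pairs the smallest exact p is 2/4 = 0.5 for signed-rank and 2/6 = 0.33 for Mann-Whitney, so neither could reach 0.05.

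**Conclusion.** The point holds in this form: for pre/post uptake in the same participants, sections 3 and 10.2 offer an independent-samples rank test as the alternative to the paired t, with no selection rule. That the test does not match the design follows from the documents alone. The size of the consequence does not. It rests on an assumed correlation, effect size and normal data, and runs from almost nothing at low correlation to a large loss at high correlation with a moderate effect. Severity is moderate: a stated analysis of the primary outcome needs correcting, but in a descriptive pilot where a suitable test is also named.

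**What to change.** In section 3 (Evaluation of data) and section 10.2, replace the pre/post sentence so that:

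1. the main analysis reports each participant's change and the mean within-participant change (or log ratio) with a 95% CI from the paired t;
2. the exact Wilcoxon signed-rank test replaces Mann-Whitney U as the stated non-parametric check, reported alongside the main analysis and not chosen after seeing the data;
3. the text notes that signed-rank cannot reach two-sided p < 0.05 with five or fewer pairs (minimum 0.0625);
4. Mann-Whitney U is kept only for between-species comparisons, applied to change scores.

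The cost is wording in two sections, with no new data, visits or burden on participants. The one drawback is that signed-rank is uninformative within small species subgroups, which is why the estimate and its interval should lead.

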## **11. SOURCE DOCUMENTS AND ACCESS**

Upon request, the investigator(s)/institution(s) will permit direct access to source data/ documents for trial-related monitoring, audits, HREC review, and regulatory inspection(s) by the Sponsor (or their appropriately qualified delegate) and Regulatory Authorities provided this is feasible from a technical standpoint. Direct access includes examination, analysis, verification and reproduction of records and reports that are important to the evaluation of the study.

## **12. ADMINISTRATIVE PROCEDURES**

### **ETHICAL CONSIDERATIONS**

The amount of blood to be sampled in the study is not considered to be excessive in healthy adult participants. This study will be carried out according to the Declaration of Helsinki, the NHMRC National Statement on Ethical Conduct in Human Research (2007) and the Notes for Guidance on Good Clinical Practice as adopted by the Australian Therapeutic Goods Administration (2000) (CPMP/CH/135/95) and the ICH GCP Guidelines.

### **ETHICAL REVIEW COMMITTEE**

This Protocol will be submitted for approval to QIMR-B HREC, Clinical Trial Protocol Committee. This protocol will then be submitted for executive approval from RBWH HREC. Following this the HIRF Scientific Advisory Committee will review the Protocol and QIMR-B HREC assessment(s) in order to facilitate expedited Site-Specific Approval from the RBWH/Metro North HREC.

Written approvals will be obtained before volunteers are recruited and participants are enrolled. The Investigators will receive all the documentation needed for submitting the present Protocol to the HREC.

It is the responsibility of the Investigator to report study progress to the HREC as required or at intervals not greater than one year.

#### REGULATORY AUTHORITIES

This is an EXPLORATORY STUDY to run in parallel to an existing MAIN study clinical trial. The investigation uses the application of imaging using a standard radiotracer at standard dosages that is widely used in the clinical setting. This is administered as per existing local institution processes. Due to the unique nature of radiopharmaceuticals, facilities are able to extemporaneously produce and administer FDG onsite for their own purposes. The RBWH Nuclear Medicine department has TGA approval for manufacture of this radiotracer (Appendix F). This radiotracer is not ARTG listed for this facility, but is approved for GMP production and commercial sale from this manufacturer to other facilities within the state of Queensland. Following discussion with the TGA and study sites, this EXPLORATORY STUDY has a CTN registration for the **regulatory purpose** of accessing the standard radiotracer  $^{18}\text{F}$  FDG in a manner that ensures prospective record keeping and transparent usage. This includes processes for AE reporting as documented below.

A Nuclear Medicine Independent Medical Advisor has been nominated to ensure participant safety, to provide advice and ongoing review of any SAEs that may be related to EXPLORATORY STUDY activities. No DSMB has been nominated given the low risk nature of this small population EXPLORATORY STUDY. Participants will receive a copy of a current FDA template for  $^{18}\text{F}$  FDG product information (Appendix G), as no generic equivalent exists in Australia.

#### INFORMED CONSENT

Before recruitment and enrolment into the study, each prospective participant must be given a full explanation of the nature and purpose of the study, and a copy of the Participant Information Sheet and Consent Form to review. This form complies with the consent form requirements outlined in the TGA guidelines. Once the essential study information has been provided, and the Investigator is assured that each individual volunteer understands the implications of participating in the study, the participants will be asked to give consent to participate in the study by signing the informed consent form. The consent form shall be signed and dated by the appropriate parties. A notation that written informed consent has been obtained will be made on the participants' MAIN study file. The completed consent forms will be retained by the Investigator and a copy of these will be provided by the Investigator to the participant.

#### PARTICIPANT RE-IMBURSEMENT

Participants who are found eligible and complete the study will be compensated \$160 for their time. This is in addition to MAIN study compensation.

#### EMERGENCY CONTACT WITH INVESTIGATORS

All participants will be provided with a Participant Information Sheet and Informed Consent Form with contact details of whom to contact in the case of an emergency related to the EXPLORATORY STUDY.

Participants will also be provided with a contact card as per the MAIN study.

#### NOTIFICATION OF PRIMARY CARE PHYSICIAN

Where it is deemed appropriate by the investigator(s), study doctor and/or reporting radiologist a letter will be sent to the physician stating the nature of the EXPLORATORY STUDY including any adverse events or incidental findings. A copy shall be retained by the study site as part of the MAIN study participant file.

#### PROTOCOL AMENDMENTS

The Investigator must not modify the Protocol without first obtaining the agreement of QIMR Berghofer in writing. No changes (amendments) to the Protocol may be implemented without prior approval of QIMR Berghofer and the appropriate HREC. If a Protocol amendment requires changes to the Informed Consent Form, the revised Informed Consent Form, prepared by the Investigator, must be approved by the appropriate HREC.

#### PROTOCOL DEVIATIONS

All protocol deviations must be reported to the principal investigator. Protocol deviations will be assessed for significance by the principal investigator. Those deviations deemed to have a potential impact on the integrity of the study results, patient safety or the ethical acceptability of the trial will be reported to the HREC prior to completion of participant enrollment. Where deviations to the protocol identify issues for protocol review, the protocol may be amended as above.

#### RETENTION OF OTHER STUDY SPECIFIC SAMPLES

Electronic imaging data will be retained as per HIRF guidelines. No other samples will be collected.

#### INSURANCE AND INDEMNITY

This EXPLORATORY STUDY is an observational study to run parallel with existing MAIN study clinical trials. There are no specific expected SAEs from participation requiring indemnity, however in the event of an AE that is deemed related to EXPLORATORY STUDY participation (following Investigator and medical monitor review) the sponsor holds No-Fault Compensation for Clinical Trials insurance policy for this study. The site HIRF is part of the RBWH campus.

The MAIN study holds a No-Fault Compensation for Clinical Trials insurance policy.

#### FINANCIAL DISCLOSURE AND CONFLICT OF INTEREST

Nil conflicts of interest identified or disclosed.

### **13. DATA HANDLING, RECORD KEEPING AND PUBLICATION POLICY**

#### DATA CONFIDENTIALITY

Only the investigators, designated staff and designated MAIN study staff will have access to information that identifies a study participant.  
All MAIN study participants will be assigned a unique identifier.  
Participant identifiers in this EXPLORATORY STUDY will be consistent with those used in corresponding MAIN studies.

#### DATA CAPTURE METHODS

All imaging data will be collected in accordance with site-specific HIRF protocols.

#### TYPES OF DATA

Imaging data, reports and quantitative imaging metrics will be electronically stored in accordance with HIRF guidelines.

#### RECORD KEEPING

All study related documents and records are to be retained for a minimum of fifteen years after MAIN study completion. Written agreement from the Sponsor must precede destruction of the same. In cases where HIRF guidelines preclude the storage of source imaging data, data will be transferred to the sponsor for storage.

#### PUBLICATIONS POLICY

Publication and reporting of results and outcomes of this trial will be accurate and honest, undertaken with integrity and transparency and in accordance with QIMR BERGHOFER's Policy on Criteria for Authorship. Publication of results will be subjected to fair peer-review. Authorship will be given to all persons providing significant input into the conception, design, execution or reporting of the research according to QIMR BERGHOFER Policy on the Criteria for Authorship.

